**In Depth Interviews**

In-depth individual interviews will also be conducted using a semi-structured interview guide. We will conduct interviews with 30 randomly selected households in the intervention arm during the study split by site, and 30 different randomly selected households after all follow-ups have been completed, split by site. We will also do interviews with 30 randomly selected non-intervention households during the study. In total, we aim to conduct 90 interviews across both arms. Interviews will explore household members’ perceptions and acceptability of being visited at home by healthcare personnel and attempt to ascertain in the intervention arm, how they were perceived and if any suggestions in the process of visiting and follow up could be made.

The interviews will be conducted with available household members who are over >18 years by trained study personnel for approximately 30 minutes, in the participant’s language of choice, taped and transcribed. The interviews will be conducted one on one so as to avoid having individual responses influenced by other household members

## Outcomes

*Primary trial outcomes*

1. Comparison between trial groups of TB FREE SURVIVAL from two months after randomisation – to the final ascertainment visit among all household members identified at baseline – a total of 13 months. We will measure this in two ways; firstly, including TB irrespective of the diagnostic method and secondly, including only bacteriologically-confirmed cases of TB.

*Secondary trial outcomes*

1. Comparison between trial groups of the incidence of all-forms of TB over months 2-15 among household members identified at baseline
2. Comparison between trial groups of the proportion of TB cases with diagnostic delay (defined as number of days between onset of symptoms and diagnosis of anti-tuberculosis treatment) among household members identified at baseline and diagnosed with TB between baseline and month 15
3. Comparison between trial groups of the prevalence of TB infection measured by tuberculin skin test reactivity >10mm at month 15 among household children identified at baseline and aged under 14 years of age. Analysis will be done overall and stratified by age.
4. Comparison between trial groups of the prevalence (reported as a percentage of those tested) of previously undiagnosed and untreated HIV infection among household members identified at baseline and again at month 15.
5. Comparison between trial groups of the cumulative incidence of all-cause mortality among all household members identified at baseline between baseline and month 15.
6. Comparison between trial groups of the cumulative incidence of TB- and HIV-related non-traumatic mortality among all household members identified at baseline between baseline and month 15.
7. Estimation of the cost-effectiveness of the intensified housed TB and HIV case-finding and prevention activities compared to the enhanced standard of care from a societal perspective.

*Exploratory outcomes*

1. Cohort analysis of the incidence of bacteriologically-confirmed, and all-forms of tuberculosis among intervention group household members receiving and not receiving isoniazid preventive therapy stratified by HIV serostatus.
2. Cohort analysis of the proportion of household members in the intervention group with previously undiagnosed HIV infection identified at baseline who successfully initiate antiretroviral therapy by month 15.
3. Estimation of the fraction of TB transmission to household members attributable to household exposure to TB index cases by analysis of whole genome sequences of sputum TB isolates (*Subject to further funding being secured)*

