# Objectives

**Primary objectives:**

1. To assess the impact of the intensified household case-finding strategy on:
   1. TB free survival among all household contacts
   2. Prevalence of TB infection in household contacts under 14 years of age.
2. To assess the cost effectiveness of IHCS compared to the enhanced standard of care.

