This is an open study and we cannot blind index cases, their households, or study field research teams to allocation. However, investigator blinding will be maintained until final analysis – no interim analyses which reveal results of the study or provide an indication by group lab results or other outcomes will be provided to site staff or an investigator (apart from the trial statistician). The trial will be unblinded by the trial statistician only to the closed part of the data safety management board (DSMB) meetings, on completion of all trial activities and data cleaning, or if there is agreement to prematurely halt the study because of safety, or other participant or health service concerns, futility, or because the trial overall objective has been met prior to full recruitment or follow up.

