# Statistical Methods

### Sample size

Assuming a mean household size of 5.5 and household TB incidence the mean of that reported for each district, a sample size of 1,200 index cases in each district (2,400) in total, will provide 80% power at an alpha of 0.05 for the study to detect a 30% overall difference in TB free survival between groups with intracluster correlation coefficient of k=0.3. Routine TB data from both sites (Capricorn and Matlosana) suggest that they diagnose and treat at least double this number per annum.

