### Statistical analysis

All statistical analysis will be conducted using R (The R Foundation for Statistical Computing, Vienna). All study data cleaning and analysis procedures will be fully documented in reproducible formats. Final, anonymised study datasets will be made available though an open access data repository based at the University of Liverpool UK to facilitate replication of analysis, and secondary analysis.

All analysis will be done on an intention to treat basis, with denominators comprising of households and household members randomly allocated to trial groups.

We will compare baseline household-, and index case-, and household members-level socio-demographic and clinical characteristics between allocated trial groups using absolute numbers and proportions for categorical variables, and means and standard errors, or medians and interqualitile ranges for continuous variables.

The following situations will be considered unbalance in baseline covariates between the two intervention groups:

- More than 5% difference between the two arms in: % male and proportion of index cases with bacteriologically-confirmed pulmonary tuberculosis.
- More than 5 years difference in mean age.
- More than 1 person difference in mean number of household members

If there is no unbalance in covariates, study conclusions will be based on the unadjusted analysis described below. Otherwise, study conclusions will be based on analysis adjusted for imbalanced covariates as described below.

The primary trial outcome (*TB free survival – both bacteriologically-confirmed TB, and all forms of TB - among household contacts identified at baseline between months 2 and 15*) will be estimated by a rate ratio and 95% confidence interval, with a 2-sided p-value<0.05 considered a statistically significant difference.

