Statistical analysis will be conducted using R (The R Foundation for Statistical Computing, Vienna, Austria) or Stata (StatCorp, College Station, Texas, USA). All analyses will employ statistical methods that allow for within-cluster (household) correlations. For all analyses, a 2-sided p-value<0.05 will be considered a statistically significant difference. No adjustment will be made for multiple testing.

Although baseline imbalance between the two intervention groups is unlikely due to the large sample size of this cluster randomised trial, the following situations will be considered as demonstrating imbalance in baseline covariates:

• More than 5% difference between the two arms in: % male and proportion of index cases with bacteriologically-confirmed pulmonary tuberculosis.

• More than 5 years difference in mean age.

• More than 1 person difference in mean number of household members

If there is no unbalance in covariates, study conclusions will be based on the unadjusted analysis described below. Otherwise, study conclusions will be based on analysis adjusted for imbalanced covariates as described below.

For the primary trial outcome (TB free survival), Poisson regression with random effects to account for clustering at the household level, will be used to estimate a rate ratio, 95% confidence interval and p-value for the effect of the intervention. To allow for the stratified randomisation by district, a fixed effect term for district will be included in the regression model. Where imbalance exists between trial groups (as defined above), these covariates will also be included in the regression model.

Analysis of secondary- and exploratory outcomes will follow a similar approach, except where binomial outcomes are assessed (e.g. proportion of child household members with MTB infection; proportion of household members with undiagnosed or untreated HIV), in which case we will use logistic regression with random effects to account for household clustering. For secondary outcome 5 (community HIV load), we will calculate this as the fraction of HIV-positive individuals with a measured viral load who have detectable viraemia multiplied by the number of individuals testing HIV-positive and divided by the total population with a measured HIV status.

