**Data and Safety Monitoring Board**
We will establish a Data and Safety and Monitoring Board (DSMB) comprising of external experts, including a statistician experience in cluster-randomised controlled trials in sub-Saharan Africa, a clinical scientist experienced in TB management, and a lay member. The DSMB will meet four times: once prior to commencement of study activities; twice during the 15 month trial activity period, and once following completion of analysis. At each meeting, the DSMB will review a Trial progress report describing rates of recruitment and uptake of trial interventions, outcomes, and serious adverse events recorded. Because of the short duration of study activities, and the low potential for harm, interim analysis will not be performed.

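### The primary outcome has two versions, both judged at 0.05, and no rule says which decides (about 6.5–9% error if either suffices); the protocol also contradicts itself on child infection and early halting

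*Protocol*

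**What the plan says.** **Two versions of the primary outcome.** The Outcomes section says of TB-free survival: "We will measure this in two ways; firstly, including TB irrespective of the diagnostic method and secondly, including only bacteriologically-confirmed cases of TB". The Executive Summary makes the same split, with a hard-copy laboratory confirmation as the second version.

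**Significance level.** The Statistical analysis section names both versions as the primary outcome, to be estimated by a rate ratio, "with a 2-sided p-value<0.05 considered a statistically significant difference". The later subsection on statistical analysis of outcomes applies the same threshold to all analyses and adds: "No adjustment will be made for multiple testing". The Sample size section uses a single figure: the design "will provide 80% power at an alpha of 0.05". Effectiveness is tied to the primary outcome, in the singular, without saying which version is meant.

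**Child infection.** The primary objectives include "Prevalence of TB infection in household contacts under 14 years of age", and the hypothesis that closes the Background names it beside TB-free survival. The outcome lists in the Executive Summary and in Outcomes place it among the secondary outcomes: "Comparison between trial groups of the prevalence of TB infection measured by tuberculin skin test reactivity >10mm at month 15".

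**Early halting.** The section on randomisation, allocation and blinding lists grounds for unblinding and a premature halt. They include futility, or "because the trial overall objective has been met prior to full recruitment or follow up". The Data and Safety Monitoring Board section says "interim analysis will not be performed", although the board meets twice during trial activity and its report covers outcomes.

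**The concern.** A trial sized on one alpha of 0.05 has a 5% false positive rate only if one test, or one stated rule, decides it. Here two tests at 0.05 bear on the primary claim. If the two versions disagree at the end, the protocol gives no way to say whether the trial succeeded. A sponsor could in good faith rest the conclusion on the significant one, and readers could not tell whether that choice had been made in advance.

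The two contradictions raise a related doubt about what the trial may conclude. A favourable child result could be reported as meeting a primary objective or as a secondary finding. A halt because the objective has been met would need a between-arm comparison that another section says will not take place.

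**Working it through.** **Inputs.** From the protocol: two versions; two-sided 0.05 for each (critical value 1.960); no adjustment; one alpha of 0.05 and 80% power with 2,400 households. Assumed, because the protocol does not give it: the share of TB events that are bacteriologically confirmed, taken from 30% to 90%.

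**The plan's own figure.** One two-sided test at |z| > 1.960 has a 5% error rate, so the stated alpha is right if exactly one version decides.

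**Limits for two tests.** If they were independent, the error rate would be 1 − 0.95² = 9.75%. If they were identical it would be 5%.

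**Correlation of the nested versions.** Every confirmed case is also an all-forms case. For nested event counts, the correlation of the two test statistics is about √(confirmed events ÷ all events). This is an approximation that leaves household clustering aside.

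**Error rate if either version suffices.** This is 1 − P(|Z₁| ≤ 1.960 and |Z₂| ≤ 1.960), with Z₁ and Z₂ bivariate normal with correlation ρ:

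| Confirmed share (assumed) | ρ | At least one false positive |
|---|---|---|
| 30% | 0.548 | 8.9% |
| 50% | 0.707 | 8.3% |
| 70% | 0.837 | 7.6% |
| 90% | 0.949 | 6.5% |

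**Effect of deaths.** The Study Definitions do not define TB-free survival, so the protocol does not settle whether death is an event. If it is, deaths enter both versions and raise the shared fraction. For illustration, take 100 TB cases, 50 of them confirmed, and 67 deaths without TB. The shared fraction is (50 + 67) ÷ (100 + 67) = 0.70, which gives 7.6% instead of 8.3%.

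**If both versions must succeed.** The error rate is then at most 5%. The inflation therefore depends entirely on the missing rule.

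**Remedies compared.**
- Fixed sequence at 0.05: the second test is read only if the first succeeds, so the error rate stays at 5% and alpha is not split.
- Splitting alpha to 0.025 each: taking the stated 80% power as given, power falls to Φ(1.960 + 0.842 − 2.241) = 71.2%. Keeping 80% would need ((2.241 + 0.842) ÷ (1.960 + 0.842))² = 1.21 times the households, about 2,906 instead of 2,400.

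**Child infection.** The Objectives and the Background hypothesis rank it with TB-free survival. Both outcome lists rank it as secondary, and the text on analysis populations treats the under-14 analysis as a secondary outcome.

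**Early halting.** Stopping because the objective has been met requires comparing the arms before the end. The monitoring board section excludes interim analysis, and no look or boundary is given anywhere. Under Trial Procedures, non-intervention households are not contacted between the call at about one week and the final visit at 15 months. The two mid-trial board meetings are placed within a 15-month activity period. As written, little or no control-arm outcome data would exist at those meetings.

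**The case against.** The strongest reply is that the protocol never says either version suffices. These are two measurements of one outcome, all forms is listed first, and a decision rule may stand in an analysis plan that is not shown here. That is fair as far as it goes, and it is why the 6.5–9% is conditional. But an order of listing is not an order of testing, and the protocol does not leave the matter open: it attaches the threshold to both versions and expressly rules out adjustment. An analysis plan with a hierarchy would have to be reconciled with that text.

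It is also fair that the correlations are assumed and that the overlap keeps the inflation moderate.

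Two stronger readings are tempting and should be resisted:

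- A reader might count child infection as a third primary test and quote a larger error rate. The documents do not support that. Only the objectives list labels it primary, both outcome lists make it secondary, and effectiveness is tied to the primary outcome alone.
- A reader might infer repeated testing at 0.05 at each board meeting. No such test is planned, no looks are defined, and control-arm data would be largely absent at that stage. Any error rate computed for it would describe a design that the protocol does not contain.

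**Conclusion.** The point holds in this form. The protocol judges two versions of the primary outcome at two-sided 0.05, rules out adjustment, and does not say which decides or whether both must succeed. If either suffices, the family-wise error is about 6.5–9%. This rests on an assumed correlation of about 0.55–0.95, and the low end is likelier if deaths count in both versions. If both are required there is no inflation, but no such rule is written.

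The status of child infection and the grounds for early halting are real contradictions that affect what may be concluded. They are matters of consistency, and no error-rate figure belongs to either. It would go too far to say that the trial can be declared positive on any of three tests, or at any board meeting.

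**What to change.** Before unblinding:

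1. **Name one version of TB-free survival as the decisive primary** and test the other second, in fixed sequence, at two-sided 0.05. Amend the no-adjustment sentence to refer to this rule. The choice is the sponsor's. All-forms TB has more events. But the trial is open, and unconfirmed cases are taken from treatment registers, treatment cards or hospital diagnoses, which are more exposed to differential ascertainment than laboratory results.
2. **Reconcile the primary objectives with the two outcome lists** on child TB infection, so that it has one status throughout.
3. **Reconcile the halting grounds with the monitoring board section.** Either delete futility and objective-met from the grounds for a premature halt, leaving safety and the participant and health service concerns, or state a formal boundary and amend the sentence excluding interim analysis.

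The cost is protocol wording. The number of households does not change, because alpha is not split. The downside is that the second version can be claimed only if the first succeeds. If the confirmed version is made decisive, the sponsor should also check that the sample size statement applies to it, since it has fewer events and the Sample size section does not say which version was used.

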2. HIV testing with prompt initiation of both antiretrovirals and TB preventive treatment for HIV-infected contacts according to current South African guidelines,
3. Preventive therapy for tuberculin skin test-positive, HIV-negative **and** HIV-infected household contacts without active TB disease;
4. A three-month supportive follow-up visit to confirm treatment receipt, and assist those who have either not accessed care and treatment; or who have experienced problems with their treatment; or who have developed symptoms of TB in the interim.

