**Objectives**:

Primary trial outcomes are:

1. Comparison between trial groups of TB FREE SURVIVAL from two months after randomisation – to the final ascertainment visit among all household members identified at baseline – a total of 13 months. We will measure this in two ways; firstly, including all cases of where TB was diagnosed or multi drug TB treatment started, irrespective of the diagnostic method used and secondly, including only those with a hard copy of a laboratory confirmation of TB.

*Secondary trial outcomes*

1. Comparison between trial groups of the proportion of TB cases with diagnostic delay (defined as number of days between onset of symptoms and diagnosis of anti-tuberculosis treatment) among household members identified at baseline and diagnosed with TB between baseline and month 15
2. Comparison between trial groups of the prevalence of TB infection measured by tuberculin skin test reactivity >10mm at month 15 among household children identified at baseline and aged under 14 years of age.
3. Comparison between trial groups of the prevalence (reported as a percentage of those tested) of previously undiagnosed and untreated HIV infection among household members identified at baseline and again at month 15.
4. Comparison between trial groups of the cumulative incidence of all-cause mortality among all household members identified at baseline between baseline and month 15.
5. Comparison between trial groups of the cumulative incidence of TB- and HIV-related non-traumatic mortality among all household members identified at baseline between baseline and month 15.
6. Estimation of the cost-effectiveness of the intensified housed TB and HIV case-finding and prevention activities compared to the enhanced standard of care from a societal perspective. This will include comparisons of household costs and of quality of life of household members in the IHF and enhanced standard of care arms.

*Exploratory outcomes*

1. Cohort analysis of the incidence of bacteriologically-confirmed, and all-forms of tuberculosis among intervention group household members receiving and not receiving isoniazid preventive therapy, stratified by HIV serostatus.
2. Cohort analysis of the proportion of household members in the intervention group with previously undiagnosed HIV infection identified at baseline who successfully initiate antiretroviral therapy by month 15.

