**Secondary objectives:**

1. To assess the effectiveness of isoniazid preventive treatment on new cases of TB in HIV-seronegative individuals who are tuberculin skin test positive.
2. To compare the yield and costs of IHCS versus standard of care in identifying undiagnosed cases of TB and undiagnosed or untreated HIV
3. To compare rates of linkage to TB treatment between participants identified with TB through IHCS and standard of care
4. To explore perceptions and acceptability of doing home visits with household members

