**Sputum Collection**

To avoid bias related to collecting better quality sputum samples from symptomatic patients, we will collect one spot sputum sample from all household members capable of producing a sputum sample, before we ask about TB symptoms. Prior to producing a sputum specimen household members will be asked to drink a cup of water and rinse out their mouths, then take four deep breaths prior to giving a good cough effort. If small volumes of sputum are obtained, we will allow up to three hours for the collection of a spot sputum specimen. This specimen will be subjected to Xpert MTB/Rif (or the at time-of-study current version of the usual first line TB lab test in the public sector) and liquid mycobacterial culture at public sector laboratories. Single sputum specimens will be at least 3ml and at the lab will be mixed with decontaminant as per standard operating procedures in the two public sector laboratories we will send specimens to - then split into two: Xpert MTB Rif (with subsequent addition of buffer) and immediate liquid culture in the MGIT automated system as per current protocols in public sector mycobacterial laboratories. We will record the cycle threshold number of the Xpert and the time-to-positive in liquid culture. Sputum samples will be immediately stored and transported in coolboxes at 4ºC to public sector laboratories for testing. Anyone who tests positive for *M tuberculosis* will be immediately referred to their chosen public sector clinic for TB treatment initiation with a clear referral letter. For those who are Xpert MTB/Rif negative, HIV-negative and over 5 years of age a tuberculin skin test will be performed with the needle of the syringe parallel to the long axis of the arm at this initial visit and read 48 – 72 hours later using the ball-point pen to mark the widest transverse diameter measured with the reverse calliper method in millimetres. No induration will be documented as 0mm.

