**Follow-up household visit (1week after baseline household visit)**
Xpert MTB results and results of laboratory HIV testing (and CD4 counts and HbA1C as appropriate) will be communicated to participants by study staff including registered nurses at a follow-up household visit approximately one-week after the baseline assessment is completed. Participants with microbiologically-confirmed tuberculosis or diagnosed with HIV will be supported to attend their nearest local primary care clinic to register for ongoing care and treatment.

Participants who are older than 5 years of age or test HIV-negative and whose sputum tests are negative for TB and whose tuberculin skin test is negative will be dispensed the first month of IPT by study nurse and then referred for ongoing preventive treatment at their local clinics with a clear referral letter that includes all results. Additionally all those participants who are less than 5 years of age or are HIV-positive and sputum tests are negative for TB will be dispensed the first month of isoniazid preventive therapy by study nurses, Linkage to care will be confirmed by collection of referral cards at study facilities by study staff. Home tracing to encourage re-entry to care will be undertaken on three occasions for participants who do not attend clinics within 2 weeks of referral.

Should any liquid TB culture be resulted positive after this visit, a visit will be made to the few anticipated households from where this result was taken to inform the patient and refer him/her for TB treatment.

| **Age of household member** | **HIV status** | **TST Required** | **Active TB disease** | **TB HH contact** | **IPT initiated** | **Study procedure** |
| --- | --- | --- | --- | --- | --- | --- |
| Child < 5 years | POSITIVE on ART or not | NO | NO | YES | YES | Initiate 1 month IPT |
| Child ≥5 years, adult or adolescent | POSITIVE on ART or not | NO | NO | YES | YES | Initiate 1 month IPT |
| Child < 5 years | NEG | NO | NO | YES | YES | Initiate 1 month IPT |
| Child ≥5 years, adult or adolescent | NEG | YES | NO | YES | YES | Initiate 1 month IPT |

Table 1. IPT initiation for household contacts without TB symptoms

*Final intervention household visit (3 months after baseline household visit)*

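### Secondary objective 1 concerns isoniazid in HIV-negative, skin-test-positive contacts, but the only listed isoniazid comparison is split by HIV alone and so is confounded by the skin test that governs receipt

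*Protocol*

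**What the plan says.** Under Secondary objectives, item 1 reads: "To assess the effectiveness of isoniazid preventive treatment on new cases of TB in HIV-seronegative individuals who are tuberculin skin test positive". No outcome is defined for that population. The outcome that deals with isoniazid and TB is exploratory outcome 1, a cohort analysis "among intervention group household members receiving and not receiving isoniazid preventive therapy stratified by HIV serostatus". The outcome list in the Executive Summary has the same contrast: "receiving and not receiving isoniazid preventive therapy, stratified by HIV serostatus".

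Who gets isoniazid is described in three places:
- Executive Summary, intervention component 3: "Preventive therapy for tuberculin skin test-positive, HIV-negative" contacts, and HIV-infected contacts, without active TB.
- Follow-up household visit, on older or HIV-negative contacts: those "whose tuberculin skin test is negative will be dispensed the first month of IPT by study nurse".
- Table 1: for HIV-negative contacts aged 5 or over, a skin test is required and isoniazid is started. No result is named as the criterion.

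The baseline test is limited by the Sputum Collection section: "For those who are Xpert MTB/Rif negative, HIV-negative and over 5 years of age a tuberculin skin test will be performed". Young children and HIV-positive contacts need no test; the follow-up visit text says that those "less than 5 years of age or are HIV-positive and sputum tests are negative for TB will be dispensed the first month" of isoniazid.

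The Statistical analysis section says exploratory outcomes follow the approach of the primary outcome: a district term, and "Where imbalance exists between trial groups (as defined above), these covariates will also be included in the regression model". The covariates checked are sex, age, household size and the index case's bacteriological confirmation. Skin-test status is not among them.

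**The concern.** The skin test is both the rule for giving isoniazid and a marker of TB risk. A comparison of receivers with non-receivers that ignores it is confounded by indication, and stratifying by HIV does not help inside the HIV-negative stratum. That stratum also mixes in children under 5, who receive isoniazid untested, and non-receivers who were not given it because they had TB at baseline. The enhanced standard-of-care arm has no planned baseline skin test, so it cannot supply a skin-test-positive comparator.

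The Background argues for offering isoniazid to HIV-negative adults and older children although national guidelines do not include this. A misleading answer to this objective would therefore bear on policy, in whichever direction it erred.

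**Working it through.** The protocol gives no figure for this analysis, so there is none to reproduce. The mismatch of populations is textual and needs no arithmetic. What follows sizes the possible bias in HIV-negative contacts aged 5 or over, leaving out the untested under-5s.

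**Assumptions (none in the protocol).** Share skin-test positive p = 0.4 to 0.6. Uptake among those offered u = 0.8. Untreated TB rate ratio, positive to negative, k = 2 to 4. True isoniazid rate ratio θ = 0.60.

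**If skin-test-positive contacts are treated.** Non-receivers are the negatives plus the positives who do not start:

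observed ratio = θk ÷ {[(1−p) + (1−u)pk] / [(1−p) + (1−u)p]}

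For p = 0.4, k = 2: 1.2 ÷ (0.76/0.68) = 1.07.

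| | k = 2 | k = 3 | k = 4 |
|---|---|---|---|
| p = 0.4 | 1.07 | 1.46 | 1.77 |
| p = 0.6 | 0.98 | 1.23 | 1.42 |

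At full uptake the observed ratio is θk, so it passes 1 once k exceeds 1/θ (1.67 for θ = 0.60). Wider inputs show that reversal is not inevitable. With θ = 0.4, k = 1.5 and full uptake the result is 0.60, which is dilution only. With p = 0.7, u = 0.5 and θ = 0.60 it is still 0.95 at k = 5.

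**If skin-test-negative contacts are treated.** Non-receivers are the positives plus the negatives who do not start:

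observed ratio = θ ÷ {[pk + (1−p)(1−u)] / [p + (1−p)(1−u)]}

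- p = 0.4, k = 2: 0.60 ÷ (0.92/0.52) = 0.34.
- p = 0.6, k = 4: 0.60 ÷ (2.48/0.68) = 0.16.

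A true 0.60 would thus look like 0.16 to 0.34. A drug with no effect (θ = 1) would show 0.67 to 0.20 for k = 1.5 to 5 at full uptake.

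**After restriction to skin-test-positive contacts.** The skin-test term drops out and the ratio is θ, provided starters and non-starters are otherwise alike.

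**Events in the restricted analysis.** Equal allocation of the planned 2,400 households is assumed, giving 1,200 × 5.5 = 6,600 members in the intervention arm. A further assumption is that 60-75% of them are HIV-negative and aged 5 or over. The Background's 700 per 100,000 per year is taken as the untreated average. The rate in positives is then 700k / [(1−p) + pk], which is 875 (p = 0.6, k = 2) to about 1,270 (p = 0.4, k = 4). Over 13 months:

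- Low: 6,600 × 0.60 × 0.4 × 0.0100 × 13/12 = 17 (k = 2).
- High: 6,600 × 0.75 × 0.6 × 0.0100 × 13/12 = 32 (k = 4).

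These are cases at untreated rates. The 20% who do not start contribute about 3 to 6. The starters contribute 17 × 0.8 × 0.6 = 8 to 32 × 0.8 × 0.6 = 15. Ignoring clustering, the standard error of the log ratio is √(1/8.2 + 1/3.4) = 0.64 to √(1/15.4 + 1/6.4) = 0.47. An estimate of 0.60 would carry a 95% interval of about 0.17 to 2.1 at the low end and 0.24 to 1.5 at the high end.

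**The case against.** **The outcome is labelled exploratory, the protocol does not tie it to secondary objective 1, and an analysis plan could add the skin test.** The first two parts are true, and the randomised primary comparison is untouched. But no other listed outcome could serve the objective, and the protocol names HIV as the stratifier in two places. The planned adjustment looks at imbalance between arms, which says nothing about receivers and non-receivers within one arm.

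**The two-month rule already acts as a landmark.** This stands in part. Isoniazid is dispensed about a week after the baseline visit, and Study Definitions restricts incident confirmed TB to specimens taken at least two months after baseline contact. Contacts helped to start at the three-month visit are still unhandled, and the definition of unconfirmed incident TB does not repeat the two-month limit.

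**A reader might infer that a protective drug will look useless or harmful.** The protocol does not support that. It holds only if skin-test-positive contacts are treated, and even then only for some inputs. Table 1 cannot be cited for that rule, because it names no result.

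**A reader might also infer that the plan simply sets positives against negatives.** It does so only approximately, and only in HIV-negative contacts aged about 5 or over. Positives who do not start join the non-receivers, untested young children join the receivers, and HIV-positive contacts are treated without a test.

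**The restricted comparison is too small to be useful.** This stands as a limit on the claim. With about 3-6 events in non-starters there is little room for covariate adjustment, and the choice to start remains confounded.

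**Conclusion.** The point holds as a mismatch between an objective and the only comparison that could serve it. Followed as written, the plan gives a contrast confounded by skin-test status in HIV-negative contacts aged about 5 or over. That conclusion rests on the text alone.

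Direction and size are less certain. Under the Executive Summary rule, a true 0.60 would appear as about 0.98-1.77; under the follow-up visit wording, the benefit would be overstated. Both results depend on assumed prevalence, uptake, risk gradient and drug effect. The event count of 17-32 also assumes the share who are HIV-negative and aged 5 or over, and applies to both districts a rate that the protocol reports for a high-burden setting, so it may be generous.

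The change should be made, but it concerns a secondary objective and an exploratory outcome, not the trial's main conclusion.

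**What to change.** 1. Reconcile Executive Summary component 3, the follow-up visit text and Table 1 on how the skin-test result relates to isoniazid. The analysis cannot be specified until they agree.
2. In exploratory outcome 1, both in the Executive Summary and under Outcomes, define the analysis that serves secondary objective 1 as HIV-negative intervention-arm contacts with a positive baseline skin test and no TB at baseline. Compare those who started isoniazid with those who did not. Count time from a stated landmark or use time-varying exposure, so that later starters are classified correctly.
3. Reword secondary objective 1 as a descriptive, non-randomised association within the intervention arm, and state the expected number of events.

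The cost is protocol wording and a changed analysis population; the data are already planned in the intervention arm. The price is a smaller comparison with few events, little scope for covariate adjustment and a more modest claim. If the reconciled text leaves few treated people in this population, the objective itself would need to be reconsidered.
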